### Participant Timeline

Each participant will have to undertake pre-and post fMRI and resting-MRI scan in this trial. They will undertake a 2-week TPS treatment, with three 30-min sessions each week. It takes ~1 month to complete all the interventions, and all participants will be followed-up at a 3-month period after the last TPS treatment session.

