### Trial Design

In this proposed study, we will use a single-blind randomised controlled trial design with two-armed repeated measures. The trial design complies with the Consolidated Standards of Reporting Trials (CONSORT) statement (61). In our two-armed design, we will use TPS as an intervention group and a waitlist control group. At the same timepoints, we will appropriately compare the effect of the TPS treatment between those who received it in the intervention group and those who did not receive it in the waitlist control group (62). Both groups were measured at baseline (T_1_), immediately after the intervention (T_2_), and at the 3-month follow-up (T_3_). A total of 30 community-dwelling subjects, aged 18 and above, will be recruited. All subjects will be computer randomised into either the intervention group or the waitlist control group, balanced by gender and age on a 1:1 ratio. All subjects in each group will have to undertake fMRI before and after six 30-min TPS sessions, which will be completed in 2 weeks' time. Baseline measurements and post-TPS evaluation of the psychological outcomes (i.e., depression, cognition, anhedonia, and IADL) will also be conducted on all participants. Based on the previous studies, a 3-month follow-up is sufficient to assess the long-term sustainability of the TPS intervention (60).

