### Interventions

#### Explanation for the Choice of Comparators

All participants involved will receive TPS treatment. The comparing groups were referred to as the waitlist control group. At the same timepoints, we will appropriately compare the effect of the TPS treatment between those who received it in the intervention group and those who did not receive it in the waitlist control group (62).

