#### Intervention Description

##### Intervention (TPS)

**Purpose of the intervention**: The key tenets of the TPS intervention is neuromodulation, i.e., using ultrasound-based brain stimulation techniques to modulate the human brain in a focal and targeted manner (60). **Intervention dose**: Each participant should have the pre-treatment MRI scan performed in the University Research Facility in Behavioural and Systems Neuroscience, PolyU prior to coming to the first intervention session. All participants (both TPS group and the waitlist control group) will receive six 30-min TPS sessions (300 pulses in each session, with a total of 1,800 pulse) in 2 weeks' time (i.e., 3 sessions (Monday, Wednesday, and Friday) per week, a total of 3 h). Participants will be followed up at a 3-month period after the intervention (Figure 5). We believe that a 2-week TPS intervention will be sufficient enough to test the effects of TPS on depressive symptoms (60).

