### Statistical Methods

#### Statistical Methods for Primary and Secondary Outcomes

##### Data Analysis Plan

Data will be analysed by the SPSS for Windows, version 27. The normality of the primary outcome (depression) scores will be tested by the Kolmogorov-Smirnov test. If significant differences between sociodemographic variables are found, covariates will be used as a control or confounding variables in the main analysis. For Objective 1, multilevel modelling analysis will be used to investigate changes in the outcome measures (depression) at each time interval (2 weeks and 3 months) with respect to their baseline measurements to examine the effects of TPS. A two-level model will be built, with repeated time points at level 1 and respondents at level 2. The baseline difference between groups will be tested using the Wald test based on the regression coefficient estimates of the indicator. The changes in the outcome measures over time will be included in the fixed part of the model to estimate change from baseline to 2 weeks and from baseline to 3 months. To assess the effects of TPS over time, interaction terms will be included in the fixed part of the model. The significantly different demographics between groups identified in step one of the analysis and other possible confounders will be adjusted by including them in the main-effect model. The within-respondent random effects of the outcome measurements will be taken into account by the level-2 variance in the model. For Objectives 2, 3, and 4, pairwise comparison and other hypotheses on the intervention effects will be tested using a generalised Wald test with an adequate degree of freedom from the modelling analysis (70). The same model, which will be conducted separately for each outcome, will be used to investigate the effect of interventions on secondary outcome measures. To assess the effects of TPS, an intention-to-treat (ITT) analysis will be performed on all participants who undergo random allocation. A multiple imputation method will be used to handle missing data. The pooled results of the multilevel analyses with five multiple imputations will be presented. A sensitivity analysis will be performed by comparing results from analysis datasets with and without missing data imputation. In all tests, significant differences between groups will be detected with a 95% CI, and *p*-values of < 0.05 (two-tailed) will be considered significant. For Objective 5, the neurological rs-fMRI data, longitudinal VBM will be used to examine whether TPS produces local changes in grey matter. Specifically, relative local increases and decreases between pre- and post-intervention scans will be compared within and between study groups. The diffusion MR data will be analysed using the diffusion tensor model. After a mathematical diagonalization process, the eigenvectors and eigenvalues describing the tensor ellipsoid will be determined. Then, two standard diffusion indices will be obtained which are the following: (1) the apparent diffusion coefficient and (2) the fractional anisotropy. DTI scans pre- and post-treatment will permit the assessment of changes in axial diffusivity, with lower values being interpreted as the structural enhancement of white matter. For the cognitive data analysis, general linear modelling (GLM) will be used to compare the difference in performance in the forward and backward digit span, the Stroop test, the category verbal fluency test, and the TMT Parts A and B between the TPS group and the waitlist control group. Performance on the TMT between the TPS group and the waitlist control group will be analysed by one-way repeated-measures ANOVA. Participants' narrative feedback on TPS will be analysed with descriptive content analysis.

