### Limitations of This Study

There are some limitations that need to be addressed in this protocol. First, since we will execute the first pilot RCT nationwide interrogating the effects of TPS on MDD, we can only use existing NIBS studies like TMS and tDCS to act as a comparison for our findings. Since both TMS and tDCS use non-invasive neuromodulation technology by electrical stimulation, the mechanism will be somehow different from TPS which uses ultrashort ultrasound waves in the stimulation of the human brain. Thus, our findings will need to be interpreted with caution. Second, participants in the waitlist control group will be given the identical TPS intervention, albeit in different timepoints, but they will all receive the same TPS pulse/frequency/energy in this TPS trial. Third, the TPS machine itself may have a potential placebo effect which may bias the results. Fourth, there could be a potential risk of contamination if our waitlist control group utilised self-prescribed pharmaceutical input or other TCM modalities (e.g., herbal soup and acupuncture) to treat their symptoms of depression while waiting the TPS treatment. Such contamination may impact the receptivity and efficacy of our TPS intervention. Fifth, participants will be administered the same sets of psychological instruments at three different time points so there is a potential risk that some participants may recall some contents of these instruments. To prevent this, our research personnel will not provide accurate answers to these tests throughout each study phase to minimise recall bias. Last but not least, individuals with severe depression with fleeting suicidal ideas will be excluded in this study, and thus, the efficacy of TPS on these severely depressive and suicidal community-dwelling individuals will remain unknown. Future replication of a multi-centre study may adopt a double-blinded, sham-controlled RCT to philtre out the placebo effects on a larger sample.

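### As written, the 3-month and MRI between-group tests compare treated with treated participants, not the treated-versus-untreated comparison the protocol promises

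*Protocol article*

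**What the plan says.** **Comparison promised.** Trial Design and Explanation for the Choice of Comparators both say the trial will, at matching times, "compare the effect of the TPS treatment between those who received it in the intervention group and those who did not receive it".

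**Who is treated.** The same comparator section also says "All participants involved will receive TPS treatment". The Intervention (TPS) section says "All participants (both TPS group and the waitlist control group) will receive six 30-min TPS sessions". Limitations of This Study adds that "participants in the waitlist control group will be given the identical TPS intervention, albeit in different timepoints".

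**When follow-up falls.** Participant Timeline puts completion of all interventions at roughly one month and says "all participants will be followed-up at a 3-month period after the last TPS treatment session". Provisions for Post-trial Care likewise ties the 3-month assessment to participants who have finished TPS.

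**When scans fall.** Trial Design says "All subjects in each group will have to undertake fMRI before and after six 30-min TPS sessions". The Neuroimaging section describes one scan before and one after treatment.

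**What is tested.** The Data Analysis Plan uses a multilevel model with interaction terms to "estimate change from baseline to 2 weeks and from baseline to 3 months". For imaging, "relative local increases and decreases between pre- and post-intervention scans will be compared within and between study groups". The Neuroimaging section also plans a dual-regression test of between-group network differences.

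**The concern.** A waitlist arm is a control only while it is still waiting. Once it has had the same six sessions, a between-arm difference no longer estimates TPS against no TPS. It estimates earlier against later TPS. The text appears to put the waitlist arm past that point at its 3-month visit and at its second scan, while the analysis still treats both as efficacy contrasts.

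Two conclusions are at stake. Three months is one of the two change contrasts modelled for the primary outcome (HAM-D-17), and the sustainability statements in Trial Design, Plans for Assessment and Collection of Outcomes and the Discussion depend on it. A lasting benefit in both arms would give a null between-group result and could be reported as an effect that faded. A null between-group imaging result could be misread in the same way. Within-arm change remains estimable, but it has no untreated comparator to separate TPS from natural recovery.

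**Working it through.** **Step 1: the timeline.** Inputs: six sessions over 2 weeks in both arms (Intervention (TPS)); about 1 month for all interventions and follow-up 3 months after the last session (Participant Timeline); T3 at 12 weeks after the intervention (Plans for Assessment and Collection of Outcomes). The week in which the waitlist arm is treated is not given, so each reading is tried.

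- *About 1 month covers both arms in turn (assumption).* The TPS arm is treated in weeks 0–2 and the waitlist arm in about weeks 2–4. If T3 runs from the end of the TPS arm's course, it falls at week 2 + 12 = 14, which is 14 − 4 = 10 weeks after the waitlist arm's last session. If it runs from the waitlist arm's own course, it falls at week 4 + 12 = 16.
- *About 1 month is each participant's own course.* T3 is then 3 months after that participant's own last session, whenever the course began.
- *The waitlist arm stays untreated until T3.* This would give the promised comparison. But Participant Timeline says all participants are followed up after TPS, and Trial Design promises post-TPS evaluation of everyone. Limitations of This Study describes only three administrations of the instruments. If the waitlist arm's three were all untreated, its post-TPS evaluation would need visits that no section provides.

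Under the first two readings the waitlist T3 value is post-TPS. The third conflicts with the text.

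**Step 2: imaging.** Each arm has one scan before and one after TPS. No control-period scan is described. The waitlist pre/post pair therefore spans TPS, as the TPS arm's pair does.

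**Step 3: T2.** The Data Analysis Plan measures change at 2 weeks from baseline, and the comparator section refers to matching times. On that clock the waitlist arm can still be untreated at T2. The Abstract (Methods) and Plans for Assessment and Collection of Outcomes instead define T2 for both groups relative to the end of the intervention, which does not secure this for an arm treated later.

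**Step 4: size, for illustration.** The total of 30 cannot be reproduced, because Sample Size Estimation gives no effect size, SD or power; the point does not depend on it. Take 30/2 = 15 per arm (1:1) and two-sided alpha 0.05. Assume a true effect d in SD units, and let s be the share of it that the waitlist arm already carries at T3. Then:

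- expected contrast e = d(1 − s)
- SE = √(2/15) = 0.365
- power ≈ Φ(e/SE − 1.96) + Φ(−e/SE − 1.96)

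For d = 1.0:

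- s = 0: e = 1.0, e/SE = 2.74, power 78%
- s = 0.5: e = 0.5, e/SE = 1.37, power 28%
- s = 1: e = 0, rejection rate 5%

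For other assumed effects, at s = 0, 0.5 and 1:

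| d | s = 0 | s = 0.5 | s = 1 |
|---|---|---|---|
| 0.5 | 28% | 11% | 5% |
| 0.8 | 59% | 20% | 5% |
| 1.2 | 91% | 38% | 5% |

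A noncentral-t calculation for d = 1.0 gives 75%, 26% and 5%, so the pattern does not depend on the normal approximation.

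**The case against.** The strongest reply is that no sentence states when the waitlist arm is treated. Limitations of This Study says only that it happens at another time, and the flow diagram (Figure 5), to which the text refers for the schedule, is not shown here. The one-month figure sits in a description of a single participant's path and need not say anything about when the waitlist arm starts. This stands: the waitlist schedule cannot be asserted as known. A figure that kept that arm untreated until T3 would still contradict the written timeline, so reconciliation would be needed either way.

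A reader might infer that T2 is lost as well. The documents do not support that, because the Data Analysis Plan sets a 2-week interval from baseline. The wording elsewhere merely fails to guarantee it.

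A reader might also say the T3 test rejects 5% of the time whatever the truth. That needs an equal and fully persistent effect in both arms; with half carried over, the illustration gives 11% to 38%.

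Nor can regression to the mean be tied to the entry threshold by assuming that the eligibility HAM-D-17 score doubles as T1. No section says that it does.

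Finally, Objective 5 is worded as a within-participant comparison with the pre-treatment scan, and the scan schedule serves that purpose. This also stands: only the between-group imaging reading is undermined.

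**Conclusion.** The point holds for the 3-month between-group contrast and for all between-group imaging contrasts, on the text as written. Both lack the untreated comparator that Trial Design and the comparator section promise. With an equal, lasting effect in both arms the expected T3 contrast is about 0; with partial carry-over it shrinks in proportion. The power figures rest on assumed effect sizes and a simple two-sample comparison rather than the planned multilevel model, and only show the scale of the dilution. The finding does not extend to T2, which remains a valid randomised contrast if both arms are assessed 2 weeks from baseline and the waitlist arm is still untreated then. Within-arm changes can be reported but are not randomised evidence. The trial's pilot status does not remove the problem, because no analysis of treated-versus-treated data recovers the missing control.

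**What to change.** 1. Reconcile Trial Design and Explanation for the Choice of Comparators with Intervention (TPS), Provisions for Post-trial Care and Participant Timeline. State when the waitlist arm is treated relative to T2 and T3.
2. Define T2 in both arms as the common 2-week time from baseline, before the waitlist arm's first TPS session. Make it the randomised efficacy contrast for HAM-D-17 and the secondary outcomes.
3. Unless the waitlist arm is in fact untreated until T3, report T3 as uncontrolled within-participant follow-up or as early-versus-delayed TPS. Reword the sustainability statements in Trial Design, Plans for Assessment and Collection of Outcomes and the Discussion to match.
4. For MRI, choose one of two options. Either take the waitlist arm's second scan at the common T2, or keep the schedule, report uncontrolled pre/post change and drop the between-group efficacy reading.

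**Cost.** Items 1 and 3 are wording and analysis changes; item 3 gives up a controlled 3-month claim that the written schedule does not support. Item 2 may need the waitlist T2 assessment rescheduled. The first MRI option, with two scans kept, leaves the waitlist arm without a post-TPS scan and so takes that arm out of the pre/post data for Objective 5; keeping both would need a third scan. Trial Status says recruitment was completed on 30 October 2021, so rescheduling may be too late. If visits are already complete, the analysis and claim changes still apply.

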### Sample Size

#### Sample Size Estimation

To the best of our knowledge, there is only one TPS uncontrolled pilot study conducted on 35 patients with AD in Austria (60). Therefore, we cannot base on their effect size to estimate our sample size in this study. Considering the nature of our study is the first pilot RCT in using TPS in the treatment of depression, and also referenced by Beisteiner's study, we aim to recruiting 30 subjects to evaluate the efficacy of our primary and secondary outcomes in this study.

### Recruitment

Participants will be recruited *via* a mass email invitation delivered to the eligible subjects *via* collaborators in The Hong Kong Polytechnic University and University of Hong Kong. A QR code flyer will also be flagged up in communal areas in The Hong Kong Polytechnic University and University of Hong Kong campuses. A 1-h orientation session on TPS intervention will be conducted at The Hong Kong Polytechnic University and University of Hong Kong to explain the purpose and objectives of the study and to recruit potential participants on site. The research assistant will be stationed on-site in The Hong Kong Polytechnic University and University of Hong Kong to facilitate recruitment and answer immediate enquiries.

## Assignment of Interventions: Allocation

### Sequence Generation

#### Randomisation, Allocation, and Masking

All consenting participants will be listed in alphabetical order according to their surnames, and each participant will be assigned a unique study number. After baseline measurement, randomisation will be conducted by an independent statistician off-site using a stochastic minimisation programme to balance the gender, age, and depression scores of the participants. Eligible participants will be randomised into two groups using a pre-/post-test waitlist control group design. The allocation to the two groups will be 1:1.

### Concealment Mechanism

An independent statistician will use a computer-generated list of random numbers (www.random.org) to ensure concealment of randomisation. To avoid information flow, participants in both groups will be advised not to reveal their study participants to the other group, to minimise potential contamination of the effects of TPS or subject bias. The participant list will be concealed from the recruitment venues throughout the study.

### Implementation

The PI and research assistants will enrol participants, and the PI will assign participants to either the TPS group or the waitlist control group.

## Assignment of Interventions: Blinding

### Who Will Be Blinded

Trial participants from both intervention and waitlist control groups will be blinded after assignment to groupings before treatment.

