**Significance of the Study:**

Results of this study will be used to inform health policy to determine whether TPS could be considered as a top treatment option for MDD.

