### Procedure for Unblinding If Needed

Participants will be asked to guess which group they belonged to in the last TPS session to evaluate the success of blinding.

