### Data Collection and Management

#### Plans for Assessment and Collection of Outcomes

Both groups will be measured at baseline (T_1_), immediately after the intervention (T_2_), and at the 3-month follow-up (T_3_; refer to Figure 5 CONSORT flow diagram). Based on the previous studies, a 3-month follow-up is sufficient to assess the long-term sustainability of the TPS intervention (60). A trained clinician investigator who is not involved in the intervention will perform the assessments. The primary and secondary outcomes will be assessed at baseline, immediately after the intervention, and 12 weeks after the intervention.

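### The trial is labelled single-blind with participants as the blinded party, but a waitlist without sham cannot blind them after treatment starts, the guess check cannot test it, and rater masking is not stated

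*Protocol article*

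**What the plan says.** Trial Design states: "we will use a single-blind randomised controlled trial design with two-armed repeated measures". The Methods part of the Abstract uses the same label. Who Will Be Blinded gives that single blind to participants and to nobody else: "Trial participants from both intervention and waitlist control groups will be blinded after assignment to groupings before treatment".

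Explanation for the Choice of Comparators says that, at common timepoints, the comparison is between "those who received it in the intervention group and those who did not receive it in the waitlist control group". Intervention (TPS) and Limitations of This Study add that the waitlist arm later receives the same six real sessions. No sham is used. Limitations leaves that to later work: "Future replication of a multi-centre study may adopt a double-blinded, sham-controlled RCT to philtre out the placebo effects on a larger sample". It also concedes that "the TPS machine itself may have a potential placebo effect which may bias the results".

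Procedure for Unblinding If Needed sets the check: "Participants will be asked to guess which group they belonged to in the last TPS session to evaluate the success of blinding".

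On the rater, Plans for Assessment and Collection of Outcomes says: "A trained clinician investigator who is not involved in the intervention will perform the assessments".

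On the use of the results, the Abstract (Significance of the Study) says that they will inform health policy "to determine whether TPS could be considered as a top treatment option for MDD".

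**The concern.** The label claims a property that the design cannot have. A reader or evidence reviewer who sees a single-blind trial with participants as the blinded party will assume that expectancy is controlled on the participant side. Here it is not. The primary outcome (HAM-D-17) is a symptom rating that depends on what the participant reports, and one secondary outcome (SHAPS) is pure self-report. Both are open to expectancy.

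The person who could be blinded in a waitlist design is the assessor, and the article does not say that the assessor is. The planned guess might then be reported as evidence that blinding worked, although it carries no information on that question at the time that matters. At stake is how the between-group result is interpreted, and whether it can bear the policy inference in the Abstract.

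**Working it through.** The plan gives no figure on this point, so there is nothing to reproduce. The check is mainly a reading of the sections against each other.

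**Step 1: can participants be blind at a post-baseline assessment?** The intervention arm attends six 30-minute sessions with tracking glasses and a handpiece (TPS Treatment Setting and Treatment Procedures; Intervention (TPS)). During the same period the waitlist arm attends none and has no sham. Each person can tell which of these applies. Concealment Mechanism points the same way: it asks members of each group to keep their participation from the other group, which presumes that they can tell the groups apart.

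The sentence in Who Will Be Blinded could be read narrowly, as blinding only in the interval between assignment and treatment. That reading does not help. Such blinding ends before any post-baseline measurement, and the check in the next section is placed at the last session, well after that interval.

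**Step 2: can the guess test blinding at T2?** Anyone answering at a last TPS session is being given real TPS, because both arms receive the identical course at different times. The only cue to group is whether the person waited first, and each person knows that. For a waitlist member, that session falls after the untreated period compared at T2. The answer therefore says nothing about what that person believed when T2 was rated.

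**Step 3: is the rater masked?** The article separates the assessor from delivery of the intervention. It does not say that the assessor is kept unaware of allocation. Participants are asked not to disclose to the other group; nothing asks them not to disclose to the assessor. The section that lists who is blinded names participants only.

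**Step 4: scale, for illustration only.** Inputs from the document are N = 30 (Sample Size Estimation), 1:1 allocation, hence 30/2 = 15 per arm (Randomisation, Allocation, and Masking), and two-sided 0.05 (Data Analysis Plan). Two inputs are assumed and not in the document: no true TPS effect, and a shift of b SD from expectancy or rating.

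For a two-sample t-test, df = 15 + 15 − 2 = 28 and the noncentrality is b × √(15/2) = 2.739 b. The probability of a significant result is P(|T| > t₀.₉₇₅,₂₈), with T noncentral t.

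| Assumed bias b (SD) | Noncentrality | P(significant, two-sided) |
|---|---|---|
| 0 | 0 | 5.0% |
| 0.2 | 0.548 | 8.3% |
| 0.3 | 0.822 | 12.5% |
| 0.5 | 1.369 | 26.2% |
| 0.8 | 2.191 | 56.2% |

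The result is driven by the assumed b. The Data Analysis Plan specifies a multilevel model of change from baseline with interaction terms, under which the rates would differ.

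**The case against.** The best defence is disclosure. Limitations of This Study already names the placebo effect and points to a sham-controlled successor, and the trial is presented as a pilot. A waitlist without sham is a legitimate choice for a pilot. This stands: the comparator is not the fault. But the disclosure does not correct the single-blind label, the sentence saying who is blinded or the guess check, and it is not carried into the Abstract or the Discussion.

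Second, the assessor is independent of treatment delivery, and a condensed article may leave masking procedures to the full protocol. This stands in part. Independence is a real safeguard, though it is not masking, and the section that answers who is blinded lists participants only. A reader might infer that the rater is unmasked. The text does not support that; it is silent.

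Third, a reader might infer that T2 is the only comparison against untreated participants. The readable text does not say when the waitlist arm is treated relative to T3, and the flow diagram is not shown. The point does not need that claim.

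Fourth, the policy sentence is hedged: it speaks of informing a decision. That is fair, so the remedy is to qualify it.

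**Conclusion.** The concern holds. Participant blinding is claimed but cannot exist after treatment starts. The guess at the last TPS session cannot test blinding at T2. Masking of the HAM-D-17 rater is unstated. These conclusions rest on the text alone and need no assumption about effect sizes or about when the waitlist arm is treated relative to T3.

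The consequence is that the between-group contrast estimates TPS including expectancy against waiting. Rater bias is possible but not shown.

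The 12% to 26% should not be read as this trial's false-positive rate. It depends on an assumed bias of 0.3 to 0.5 SD, no true effect and a simple t-test. The documents give no basis for choosing a bias size, and 0.2 to 0.8 SD would give 8% to 56%.

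**What to change.** 1. In the Abstract (Methods), Trial Design and Who Will Be Blinded, state that participants are not blinded.
2. In Plans for Assessment and Collection of Outcomes, require the existing independent assessor to be masked to allocation, and tell participants not to disclose it to the assessor. Call the trial assessor-blinded only if that masking was actually in place. Otherwise report it as open-label with an independent rater.
3. Replace the participants' guess with the assessor's guess of allocation, recorded straight after each remaining post-baseline HAM-D-17. If those ratings are already done, drop the guess as evidence of blinding.
4. Carry the placebo limitation into the Abstract (Significance of the Study) and the Discussion, so that the contrast is read as TPS including expectancy versus waiting.

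The cost is wording, one instruction and one question on the assessor's form. No staff are added, because the separate assessor already exists. There are two limits. Trial Status says recruitment ended on 30 October 2021, so with a two-week course some or all T2 ratings may be past and items 2 and 3 may come too late for them; items 1 and 4 remain possible. Masking the rater also does not remove participant expectancy, notably on self-reported SHAPS, so item 4 is needed in any case. The price is a more modest claim.
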